### Observations

#### Dependent variable

Development of symptomatic TE in any location while receiving therapy on DFCI ALL 05–01 study. *Symptomatic TE* is defined as any objectively confirmed arterial or venous TE which was discovered as a result of investigations prompted by typical clinical symptoms (as outlined in Table 2). Screening for *asymptomatic* TE was not performed.

**Table 2 Tab2:** Definition of symptomatic TE and preferred diagnostic evaluation

	Site	Likely clinical signs and symptoms	Diagnostic method/s
CNS	Arterial ischemic stroke +/− hemorrhage	Unexplained headaches, vomiting, visual problems, or neurological deficits, seizure, drowsiness or any change in mental status	MRI/MRA Angiogram
	Sinovenous thrombosis (SVT)		MRI /MRV CT venogram
PE	Pulmonary vasculature	Respiratory problems (shortness of breath, tachypnea, dyspnea) hypoxia, chest pain, syncope “Unexplained pneumonia”	V/Q scan Spiral CT Pulmonary angiogram
DVT	Upper venous system	Swelling, pain, tenderness, erythema, dilated vessels	Bilateral venogram is “gold standard” for diagnosis especially for subclavian/brachial vessels ^a^Doppler USG sufficient for jugular vein MRV Recommend ECHO to evaluate RA
	Lower venous system		^a^Doppler USG to evaluate all sites Venogram is still the gold standard
Cardiac	Right atrial (RA)	CVL malfunction, sepsis, congestive heart failure	ECHO
CVL related	Asymptomatic CVL tip thrombi **ONLY if** the catheter tip is in RA	-	ECHO Linogram Venogram
	**Only** symptomatic CVL TE will be considered significant	Swelling, pain, tenderness, erythema, dilated vessels, CVL malfunction requiring revision or renewal, headache, swelling of face	Linogram +/− venogram &/or ^a^Doppler USG depending upon the site of thrombosis

In the presence of TE at one site recommend evaluating other sites (especially if anatomically related e.g. jugular vessels in presence of SVT) for associated asymptomatic TE, if possible

*TE* thromboembolism, *CNS* central nervous system, *MRI* Magnetic resonance imaging, *MRV* Magnetic resonance venogram, *MRA* Magnetic resonance arteriogram, *PE* pulmonary embolism, *V/Q* scan ventilation/perfusion scan *CT* computerized tomogram, *DVT* deep venous thrombosis, *USG* ultrasonogram, *CVL* central venous line

^a^Detection of echogenic material within the lumen of a vein on a gray scale and presence of partial or complete absence of flow by pulse wave or color Doppler ultrasonography

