### Assays for hemostatic factors

#### Timing of blood test

Blood samples for prothrombotic defects were collected for all patients prior to starting ALL therapy. For Hcy and Lp(a) estimation overnight fasting blood sample were used. Testing for prothrombotic defects were done on the day of the scheduled lumbar puncture avoiding additional fasting.

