#### Methods for analysis

Patient demographics, prognostic characteristics and clinical outcome will be summarized using descriptive measures expressed as mean (standard deviation) or median (minimum, maximum) for continuous variables and number (percent) for categorical variables. The analysis will adopt the intention-to-treat principle. Since TE is a safety outcome for ALL-therapy we will also perform “per-protocol” analysis. Association between categorical outcomes and groups will be assessed using Fisher’s Exact test or chi-squared test. Thrombosis-free survival will be estimated using Kaplan-Meier method. The limit for statistical significance will be set at α = 0.05. In all comparison, 95% confidence intervals (CI) of the measure of association between groups will be reported.

Logistic regression will be used to analyze data for both primary and secondary outcomes. Analysis results of regression modeling will expressed as coefficient, corresponding standard error, 95% CI and associated *p*-values. Variance inflation factors will be used to assess multi-colinearity among predictors. Model assumptions will be assessed through residual analysis. Goodness-of-fit will be evaluated using qq plots for normality and coefficient of determination and R^2^ for regression models. Some of the time dependent confounding variables like infection or CVL-related problems (which may influence the risk of TE) are unpredictable and hence cannot be adjusted prospectively. To compensate for that we will prospectively collect the information and enter in the regression model when risk factors for thrombosis are being analyzed. All analyses will be performed using SPSS 14 software (2005 SPSS Inc). Table 3 provides a summary of specific methods of analysis for primary and secondary outcomes.

**Table 3 Tab3:** Proposed Methods of Analysis

Analysis	Hypothesis	Independent variable	Outcome variable		Method of analysis
			Name	Variable type	
Primary	Presence of one or more prothrombotic defect/s increase the risk of TE	Presence of one or more prothrombotic defect	Symptomatic TE	Binary	Fisher’s Exact Test Analysis performed for overall prevalence of at least one prothrombotic defect and for individual defect.
Secondary					
Aim 1.	1.a Older age increases the risk of TE, especially in presence of one or more prothrombotic defect	Age of the patient (age < 10 years, age ≥ 10 years)	Symptomatic TE	Binary	Logistic regression

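### The TE regressions adjust for on-therapy infection and CVL problems as confounders, though some are presenting signs of TE and none can confound a pre-therapy defect; the primary Fisher test is unaffected

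*Protocol article*

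**What the plan says.** All references are to the protocol article.

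- **Outcome.** Under Dependent variable, a TE counts only if it was "discovered as a result of investigations prompted by typical clinical symptoms" and is objectively confirmed. Table 2 lists the likely signs by site. For right atrial TE they are "CVL malfunction, sepsis, congestive heart failure". For CVL-related TE they include "CVL malfunction requiring revision or renewal". The rows for CNS TE, pulmonary embolism and other deep venous thrombosis list neither CVL malfunction nor sepsis.
- **Covariates.** Methods for analysis says that "Some of the time dependent confounding variables like infection or CVL-related problems (which may influence the risk of TE) are unpredictable", and that to compensate "we will prospectively collect the information and enter in the regression model when risk factors for thrombosis are being analyzed". It sets no rule on when an episode must start relative to the TE.
- **Model.** The same section states: "Logistic regression will be used to analyze data for both primary and secondary outcomes". The primary row of Table 3, however, names Fisher's exact test of any defect against TE, with this scope: "Analysis performed for overall prevalence of at least one prothrombotic defect and for individual defect".
- **Exposure.** Timing of blood test states: "Blood samples for prothrombotic defects were collected for all patients prior to starting ALL therapy".

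**The concern.** Two separate problems follow from placing these sections side by side.

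First, for some TE sites the covariate is also a listed trigger for finding the outcome. A child whose blocked line leads to imaging and a diagnosis of CVL-related TE contributes both a CVL problem and a TE. Logistic regression on a yes/no outcome does not order one before the other. An association then arises even if line problems play no causal part.

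Second, the label of confounder is wrong for episodes that arise on therapy. The defect is measured before therapy, so a later episode cannot have caused it. Such an episode may be a consequence of TE, a step between the defect and TE, or unrelated to the defect. If defects make lines clot, adjusting for line problems removes part of the effect being sought.

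At stake are the list of TE risk factors, which is the secondary question, and any adjusted defect odds ratio reported beside the primary test. Both are meant to inform later prophylaxis trials.

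**Working it through.** The plan gives no figure on this point, so there is none to reproduce. The documents give no frequency of infection or CVL problems; every frequency below is an assumption.

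**1. How far the overlap reaches.** Feasibility anticipates 14 + 2 = 16 TE. Background puts about 50% of symptomatic TE in the CNS, 2% as pulmonary embolism and 2% in the right atrium.
- Sepsis is a listed sign for right atrial TE only: 0.02 × 16 = 0.3 expected cases. The infection part is small.
- CVL malfunction is a listed sign for right atrial and CVL-related TE. The share is not given, but it cannot much exceed 100 − 50 − 2 = 48% of TE.

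**2. Built-in odds ratio (OR) of a covariate with no causal role.** Let s be the proportion of TE cases with an episode and s0 the proportion of TE-free children with one. OR = [s/(1 − s)] / [s0/(1 − s0)].

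| s | s0 | OR |
|---|---|---|
| 0.20 | 0.10 | 0.250/0.111 = 2.25 |
| 0.30 | 0.10 | 0.429/0.111 = 3.86 |
| 0.20 | 0.05 | 0.250/0.0526 = 4.75 |
| 0.30 | 0.05 | 0.429/0.0526 = 8.14 |

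If episodes are common (s0 = 0.30) and cases carry that background rate as well as a 20% or 30% chance of presenting with one:
- s = 0.30 + 0.70 × 0.20 = 0.44, OR = (0.44/0.56)/(0.30/0.70) = 1.8
- s = 0.30 + 0.70 × 0.30 = 0.51, OR = (0.51/0.49)/(0.30/0.70) = 2.4

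The range is therefore about 1.8 to 8. With 16 TE, 20–30% is 3 to 5 children, so a handful of presenting episodes would drive the estimate.

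**3. Effect on the defect OR.** Inputs from Sample size: 20% with a defect, a 25-point difference and 11% TE overall. Risks of 31% and 6% fit: 0.20 × 0.31 + 0.80 × 0.06 = 0.11. Crude OR = (0.31/0.69)/(0.06/0.94) = 7.0. A large simulated cohort was fitted with and without the episode covariate; standard errors are scaled to 150 patients.

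| Assumed frequency of episodes | Covariate OR | Defect OR, crude to adjusted | Risk difference, crude to adjusted |
|---|---|---|---|
| Sign only: 60% of TE, 20% of non-TE, whatever the defect status | 5.9 | 7.0 to 7.0 | 0.25 to 0.22 |
| Defect also raises it: 50 to 70% in TE, 20 to 35% in non-TE | 4.1 | 7.0 to 5.4 | 0.25 to 0.19 |
| Stronger: 50 to 80% in TE, 20 to 50% in non-TE | 4.0 | 7.1 to 4.5 | 0.25 to 0.16 |

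In the first row the defect OR does not move, but the standard error of its logarithm rises from 0.55 to 0.59.

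**4. Line problem as a step on the pathway.** Here CVL problems do cause TE.
- Baseline TE risk 5%, direct defect OR 4, CVL problem OR 4, and the defect raises CVL problems from 10% to 25%. TE risks by defect and CVL problem are 0.050 (neither), 0.174 (either alone) and 0.457 (both). Without a defect: 0.90 × 0.050 + 0.10 × 0.174 = 0.062. With a defect: 0.75 × 0.174 + 0.25 × 0.457 = 0.245. The total OR is 4.9; the adjusted model reports 4.0.
- Baseline risk 4%, direct OR 3, CVL problem OR 8, 10% to 40%. Without a defect: 0.90 × 0.040 + 0.10 × 0.250 = 0.061. With a defect: 0.60 × 0.111 + 0.40 × 0.500 = 0.267. The total OR is 5.6; the adjusted model reports 3.0.

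**The case against.** The strongest case for the plan has five parts.

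- **The primary test does not use these covariates.** Correct. Table 3 fixes an unadjusted Fisher's exact test, and Sample size is built on the difference in proportions. The Table 3 rows for secondary Aims 1 and 2 list no infection or CVL term either. What remains exposed is the regression described in the text, which the protocol also applies to the primary outcome.
- **Being a presenting sign does not shrink the defect OR.** Also correct, as the first simulated row shows. Attenuation needs a further assumption, that defects raise CVL or infection episodes, and the documents give no rate for that.
- **Infection can confound.** In part. Laboratory data says that the levels of the variable defects respond to inflammation, so infection already present when the baseline sample is drawn could shift a measured defect as well as TE risk. This does not extend to episodes that begin later.
- **A sign is not the case definition.** Fair. Table 2 gives likely signs, and imaging must confirm the event. The signs still govern which children are imaged, because there is no screening.
- **Time-dependent factors are a stated question, and episode windows are detail for an analysis plan.** Studying them is legitimate. But the article does more than leave a detail open: it gives a reason for entering them, confounding, and that reason fails for on-therapy episodes.

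**Conclusion.** The point stands as a fault in the regression analyses. CVL problems, and to a small extent infection, can emerge as TE risk factors because they are how some TE present. The built-in odds ratio is about 1.8 to 8 under the assumed frequencies; its true size is unknown. Adjusting for on-therapy episodes does not remove confounding of the defect effect. It can attenuate the adjusted defect odds ratio if defects raise such episodes (7.0 to 5.4, or 7.1 to 4.5, in the simulated cases), and otherwise mainly costs precision.

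A reader might infer that the main result of the study is biased towards no effect. The documents do not support that: the primary test is unadjusted, and attenuation in the regressions rests on a link between defects and episodes that the protocol does not quantify. Nor do they support the view that infection can never confound, given what Laboratory data says about inflammation at the time of sampling.

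**What to change.** In Methods for analysis, replace the sentences on time-dependent confounding with two rules:

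1. Models that estimate the effect of a prothrombotic defect omit infection and CVL-related problems that begin after the baseline blood sample. Infection present at baseline sampling may still be adjusted for.
2. Where on-therapy episodes are studied as risk factors, only those that began before, and are separate from, the episode that prompted the TE work-up count as exposure. They enter as a time-dependent covariate in a time-to-event model. Both parts are needed: a time-dependent model alone would still count a line malfunction that led to imaging a few days later.

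The cost is a short change of text, but episode start dates must be recorded. The article promises prospective collection of the information without saying that dates are included. TE dates are already needed for the planned Kaplan-Meier estimate. Fewer episodes will count as exposure, so estimates for these risk factors will be less precise. The sample size and the primary test do not change.

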## Methods/trial design

### Scientific questions

The primary question is do identified congenital and acquired prothrombotic defects increase the risk of symptomatic TE in children with ALL receiving therapy on DFCI ALL 05–01 protocol? The secondary question is what other baseline and time-dependent factors increase the risk of clinically symptomatic TE in children with ALL receiving therapy according to DFCI ALL 05–01 protocol?

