#### Secondary Aims

To evaluate the effect of age of the patient (≥ 10 years versus <10 years), risk categorization of ALL (HR/VHR ALL versus SR ALL), baseline laboratory features (white blood cell counts, blast count and platelet count), type of ASP used (*E. coli* versus PEG), phase of therapy (Consolidation II versus other), either alone or in combination with any known prothrombotic defect/s, on the risk of development of symptomatic TE in children receiving therapy on DFCI ALL 05–01 protocol. (Since almost all our patients have CVL, we will not be able to evaluate the effect of CVL in relation with other factors).To develop a predictive model to identify children with ALL at high risk for TETo determine the prevalence of inherited and acquired prothrombotic defects in children newly diagnosed with ALL

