#### Independent variables

Presence of prothrombotic defects: Following specific prothrombotic defects were studied: deficiency of AT, PC, PS; elevated levels of coagulation factors II, VIII, IX and XI; FVL; PT and MTHFR gene mutation; elevated levels of Lp (a), Hcy and APLAPresenting laboratory features (Complete blood count, total white cell count, peripheral blast count, hemoglobin, platelet count)Age of the patient at the time of diagnosis of ALL (age ≥ 10 years, age < 10 years)Risk categorization of ALL (HR/VHR, SR)Therapy Variables: Type of ASP (*E. coli*, PEG ASP)Phase of therapy: Consolidation II versus other phases

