### Outcomes

#### Primary outcome

Diagnosis of symptomatic TE in any location while on active ALL-therapy.

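### Time-dependent risk factors (phase, infection, line problems) go into a logistic model of TE yes/no that cannot estimate phase and can badly bias the others; the primary and baseline analyses are unaffected

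*Protocol article*

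**What the plan says.** The protocol article, under Scientific questions, sets as its secondary question "what other baseline and time-dependent factors increase the risk of clinically symptomatic TE". The first secondary aim includes "phase of therapy (Consolidation II versus other" phases, and Independent variables lists "Phase of therapy: Consolidation II versus other phases".

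Methods for analysis states: "Some of the time dependent confounding variables like infection or CVL-related problems (which may influence the risk of TE) are unpredictable". It says that they cannot be adjusted for prospectively and continues: "To compensate for that we will prospectively collect the information and enter in the regression model when risk factors for thrombosis are being analyzed".

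The regression is fixed in the same section: "Logistic regression will be used to analyze data for both primary and secondary outcomes". The note under Table 3 repeats it. The outcome is "Diagnosis of symptomatic TE in any location while on active ALL-therapy", which Table 3 types as binary. The one time-to-event method is descriptive: "Thrombosis-free survival will be estimated using Kaplan-Meier method". Follow-up runs to the end of therapy, two years and one month, with earlier withdrawal for induction failure, relapse, transplantation or leaving DFCI 05-01.

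**The concern.** The protocol recognises that some risk factors change over time, then names a model that takes one outcome and one set of covariate values per child. Two problems follow.

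- **Phase.** Children who stay on therapy pass through both phase categories, so the covariate is not an attribute of the child.
- **Infection and CVL problems.** A child with TE has only the time before the event in which to acquire a prior exposure. A TE-free child has up to 25 months.

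At stake is the time-dependent half of the secondary question. Under one natural coding, a factor with no effect looks strongly protective, and a real risk factor can look protective too. The Discussion says the study's results will be used to design a prophylaxis trial.

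**Working it through.** The protocol gives no figure for this analysis. Its power statement concerns the primary Fisher comparison. That statement reproduces and is not in question: with 30 versus 120 children, normal-approximation power is 92.4% for 31% versus 6%, and 86.9% for 36% versus 11%, against a stated power above 80%.

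**Phase, by reasoning.** A one-row model could use one of two codings. Phase at the time of TE exists only for cases. Whether a child reached Consolidation II before TE or end of therapy depends on staying TE-free long enough to reach it. Neither gives TE-free children a comparable value.

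**Infection or CVL problems counted up to TE or end of therapy.** Inputs:
- Follow-up is 25 months (Study duration). All TE-free children are assumed to complete it.
- TE timing: the Abstract puts 90% of events in Consolidation but gives no months. Assumed: 90% evenly over months 1 to 8 and 10% over months 0 to 25. Alternative: all TE spread evenly over 25 months.
- The exposure rate λ per month is not in the document. Assumed: 0.014, 0.05 and 0.10.
- Exposure is independent of TE, so the true effect is nil.

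Formulas:
- TE-free, ever exposed: F = 1 − exp(−25λ).
- Cases with TE spread evenly over (a, b): A(a,b) = 1 − [exp(−λa) − exp(−λb)] / [λ(b − a)].
- Early TE: E = 0.9·A(1,8) + 0.1·A(0,25). Even TE: E = A(0,25).
- OR = [E/(1 − E)] / [F/(1 − F)]. TE incidence (11% or 15%) does not enter.

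For λ = 0.05:
- F = 1 − exp(−1.25) = 0.7135.
- A(1,8) = 1 − (0.9512 − 0.6703)/0.35 = 0.197.
- A(0,25) = 1 − 0.7135/1.25 = 0.429.
- Early: E = 0.178 + 0.043 = 0.221, so OR = 0.283/2.490 = 0.11.
- Even: OR = 0.752/2.490 = 0.30.

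| λ | F | E early | OR early | E even | OR even |
|---|---|---|---|---|---|
| 0.014 | 0.295 | 0.070 | 0.18 | 0.156 | 0.44 |
| 0.05 | 0.714 | 0.221 | 0.11 | 0.429 | 0.30 |
| 0.10 | 0.918 | 0.378 | 0.05 | 0.633 | 0.15 |

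The correct value in every row is 1. Simulation of the same set-ups agrees to within about 0.01.

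**At study size.** This simulation uses the same null and coding, with 50% of children ever exposed and 90% of TE in months 2 to 9 (assumed). Fisher p < 0.05 occurs in 77% of samples with n = 150 and 11% TE, and in 81% with n = 131 and 15% TE, against a nominal 5%. With 30%, 50% and 70% exposed, a true hazard ratio of 2 appears as an OR of 0.43, 0.37 and 0.29.

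**Exposure counted over the whole 25 months.** If TE does not change later exposure, the null OR is 1.00. If TE triples the later exposure rate (assumed), the OR is 3.3, 4.5 and 7.6 for 30%, 50% and 70% exposed with TE in months 2 to 9. With even timing it is 2.3, 2.7 and 3.3.

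**Other coefficients.** With exposure counted up to TE:
- If infection is equally frequent across a baseline factor, that factor's coefficient hardly moves. A defect OR of 6.99 becomes 7.04, and a null HR/VHR OR stays at 1.0.
- If infection is twice as frequent in HR/VHR (assumed), the null HR/VHR OR becomes 2.1. If it is 1.5 times as frequent with a defect (assumed), the defect OR goes from about 7 to about 10.

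**Events available.** Feasibility expects 14 + 2 = 16. The later figures give 131 × 0.15 ≈ 20.

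**The case against.** The article never states ever/never coding or an exposure window, and such details may sit in a fuller document. A reader might infer that the protocol prescribes ever/never coding; it does not. What stands is that logistic regression on a binary outcome is stated twice, no time-updated method is named, and one row per child leaves few alternatives. Phase fails under any of them.

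A reader might also infer that the infection and CVL odds ratios are biased however they are coded. That goes too far: whole-period counting gives 1.00 under the null when TE leaves later exposure unchanged. For CVL problems that condition is hard to defend, because Table 2 lists CVL malfunction among the signs of CVL-related TE, so exposure and outcome overlap.

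A third tempting reading is that the whole analysis is corrupted. Table 3 does not support it. The primary row uses prothrombotic defect, the aim 1 rows use age, ALL risk group and asparaginase type, and the aim 2 prediction model uses those same baseline factors. Phase, infection and CVL problems have no row. Baseline coefficients shift only if a mis-timed term is added and exposure frequency differs by that baseline factor.

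Finally, a Cox model on time since start of therapy does not rescue phase. Children on the same schedule share the same phase at each event time. In simulation with n = 150 and about 18 events, the information on phase was zero with identical schedules. It was about 0.4 when phase starts varied by half a month either way, a standard error of about 1.6 to 1.7 on the log scale. This objection holds and shapes the remedy.

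**Conclusion.** The point holds for the time-dependent part of the secondary question. The phase effect cannot be estimated with the named model, and this needs no numerical assumption. For infection and CVL problems, direction and size depend on a coding that the protocol leaves open. Counting up to TE or end of therapy gives a null OR of about 0.05 to 0.18 with early TE and about 0.15 to 0.45 with even timing. Whole-period counting gives 1.00 or an upward bias, depending on whether TE raises later exposure. The exposure rates, the months of TE and the post-TE tripling are assumptions; the 25 months and the concentration of TE in Consolidation are the protocol's own.

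The documents do not support extending this to the primary Fisher test or the baseline rows of Table 3, nor replacing logistic regression throughout.

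**What to change.** Keep the primary test and the baseline analyses in Table 3 as planned. For the time-dependent part of the secondary question, state that:

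- Infection and CVL problems are analysed in a person-period model (pooled logistic or Poisson), or in a Cox model with time-updated covariates. Only exposure dated before the TE counts, and children are censored at withdrawal.
- CVL malfunction that is the presenting sign of the TE is not counted as an exposure.
- Phase is reported as a TE rate ratio per patient-month, Consolidation II versus other phases, from person-time. It is not taken from a Cox model on time since start of therapy. A person-period model with a fine time term would meet the same near-collinearity.
- The number of terms is kept small, given about 16 to 20 events.

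The cost is analysis wording and the dating of phases, infections and line problems. TE, complications and therapy modifications are already recorded, and follow-up was still running when the article was written. No extra patients are needed. Intervals will be wide, so the results should be presented as exploratory.
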